### Recruitment

We have implemented a recruitment pathway that maps to existing arrangements for referral. Eligible participants are identified from patients who are referred by their general practitioner to a single point of access for admission to hospital at home, or who have been transferred from the Accident and Emergency Department to an Acute Assessment Unit and are assessed as suitable for hospital at home. At the point of referral to the trial each participant is provided with a Participant Information Leaflet that describes the research, and they are provided with an opportunity to discuss their questions and concerns about the research with a research nurse. Each participant has the right to withdraw from the study at any time, and if provided the reason for withdrawal will be recorded in the CRF.

### Randomisation procedure and concealment of allocation

The unit of randomisation is the individual participant, who is randomly allocated using a 2:1 ratio (2 admission avoidance hospital at home: 1 inpatient admission) by a local member of the research team who accesses Sortition, the Oxford University’s Primary Care Clinical Trials Unit’s validated in-house online randomisation system. Telephone randomisation is used if sites do not have online access. A computer-generated randomisation sequence is used, and randomisation is stratified by centre, gender and by known cognitive decline [measured by the Informant Questionnaire on Cognitive Decline in the Elderly (IQCODE)] [14]. We have opted for a 2:1 randomisation ratio to deal with the concern expressed by clinical leads that a 1:1 randomisation ratio would place unmanageable pressure on the inpatient services. The success of randomisation is being measured by the number declining to be randomised or withdrawing immediately after randomisation.

### Data collection, management and analysis

Research nurses at each site collect data from participants, and from their caregivers if the caregiver is the designated consultee, at baseline and 6 months after randomisation and at 12 months for the primary outcome, with the exception of an assessment of delirium which is at 3 and 5 days, and at 1 month after recruitment (Fig. 1). Each site completes a form to record if death has occurred, with the date; these data are collected from the medical records. Place of residence is recorded by the research nurses at each follow-up visit. Data are collected using a paper form, or directly to an electronic pro forma on Open Clinica.

**Fig. 1 Fig1:**
[figure not shown]
Study flowchart

We collect data at baseline from the patient’s clinical notes and from the clinical lead on the presenting problem that requires admission to hospital, and demographic information (age, education). We also collect data on background cognitive status using the IQCODE, a 16-item informant-based questionnaire, which can also be completed by a carer [14]; incident and persistent delirium measured by the CAM [9], co-morbidity measured by the Charlson Index [15], activities of daily living measured by the Barthel Index [11], current cognitive impairment measured by the MoCA [10], health status measured by the EuroQol five-dimension five-level instrument (EQ-5D-5 L) [12] and major health service use (for example admission to hospital, use of outpatient services and ambulances, home care/help and respite stays in a residential setting) in the 6 months prior to their current illness. If the patient appears to be burdened by the collection of baseline data we use a two-stage approach, with core data (Short IQ Code [14] and Confusion Assessment Method [9]) collected prior to randomisation and following consent, and the remaining data (Barthel Index [11], Charlson Co-Morbidity Index [15], MoCA [10], EQ-5D-5 L [12] and Health Resource Use Questionnaire) collected soon after randomisation (Fig. 2).

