**Methods/Design:**

We are conducting a multi-site randomised open trial of geriatrician-led admission avoidance hospital at home, compared with admission to hospital. We are recruiting older people with markers of frailty or prior dependence who have been referred to admission avoidance hospital at home for an acute medical event. This includes patients presenting with delirium, functional decline, dependence, falls, immobility or a background of dementia presenting with physical disease. Participants are randomised using a computerised random number generator to geriatrician-led admission avoidance hospital at home or a control group of inpatient admission in a 2:1 ratio in favour of the intervention. The primary endpoint ‘living at home’ (the inverse of death or living in a residential care setting) is measured at 6 months follow-up, and we also collect data on this outcome at 12 months. Secondary outcomes include the incidence of delirium, mortality, new long-term residential care, cognitive impairment, activities of daily living, quality of life and quality-adjusted survival, length of stay, readmission or transfer to hospital. We will conduct a parallel economic evaluation, and a process evaluation that includes an interview study to explore the experiences of patients and carers.

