**Fig. 2 Fig2:**
[figure not shown]
Participant timeline

At the 6-month follow-up point we collect data from all patients on mortality, new long-term residential care, cognitive impairment, activities of daily living, quality of life, length of stay, readmission or transfer to hospital, and on the number, type and duration of hospitalisations, the use of outpatient and day-case services, the use of community-based health care services including general practitioner consultations and practice-based nursing, medications, respite care, social care including admission to residential or nursing home, and amount of informal care received over the preceding 6 months. Unit costs will be attached to these resource volumes, using National Health Service (NHS) reference costs, Unit Costs of Health and Social Care (PSSRU), and other national data sources. We will collect the costs of the admission avoidance hospital at home intervention in collaboration with providers, and include training time and other elements. This is likely to vary between centres and we aim to collect cost information from all participating centres if possible. At 12 month follow-up we will collect data on living at home (Table 1).

**Table 1 Tab1:** Case report form

	Study period					
	Baseline	Day 3	Day 5	1 month	6 month	12 month
ENROLMENT						
Eligibility screen	X					
*Informed consent*	X					
*Screening log*	X					
Randomisation	X					
ASSESSMENT						
Assessment form	X	X	X	X	X	X
*Demographics*	X					
*Presenting problem*	X					
*Place of assessment*	X	X	X	X	X	X
*Patient status* (*‘living at home’*)		X	X	X	X	X
*Subsequent admissions*				X	X	
Adverse event log		X	X	X	X	X
QUESTIONNAIRES						
Barthel Index of Activities of Daily Living	X				X	
Confusion Assessment Method (CAM)	X	X	X	X		
Charlson Co-morbidity Index	X				X	
Health Service Use Questionnaire	X				X	
Short Form of the Informant Questionnaire on Cognitive Decline in the Elderly (Short IQCODE)	X					
Montreal Cognitive Assessment (MoCA)	X				X	
EuroQol five-dimension five-level (EQ-5D-5 L)	X				X	
Patient feedback form				X		
Difficulties in Questionnaire completion Form	X	X	X	X	X	
MISCELLANEOUS						
Death form	Completed on patient death					
Discontinuation form	Completed when a patient withdraws or is lost to follow-up					

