#### Economic analysis

We will calculate the costs in each arm of the study on an intention-to-treat basis, and will report these from a health and social care perspective; in addition we will quantify and value the cost of informal care. We will calculate quality-adjusted life years from the responses to the EQ-5D using the UK “tariff”, and use linear interpolation between baseline and 6-month values and adjusting for within-trial mortality. We will collect resource-use information on health and social care services used, including the organisation and delivery of the interventions, hospital inpatient stays and procedures, outpatient and day-case use, hospital at home durations, other consultations (including general practitioner and community nurse consultations), medications, adverse events, admission to respite care and long-term care and use of other social care. Resource use volumes will be multiplied by appropriate national unit costs such as NHS Reference Costs to derive a cost per participant. We will use an average cost in the main analysis, and information on variability will be used in sensitivity analyses and to explore the possible costs of generalising the service nationally if proven to be cost-effective. We will estimate the main cost-effectiveness measure as the net cost per quality-adjusted life year gained, for the within-trial period. In the event of a within-trial difference in mortality, we will estimate average life expectancy using information from life tables and relevant cohort studies, and estimate quality-adjusted life years gained/lost. We will handle uncertainty concerning the reported cost-effectiveness ratio using the non-parametric bootstrap and will report cost-effectiveness acceptability curves, scatters on the cost-effectiveness plane, and 95% confidence intervals (using the percentile method) around the net benefit statistic. We will conduct a sensitivity/scenario analyses for different cost perspectives, and these will include analyses in which the costs of admission avoidance hospital at home and inpatient care are allowed to vary across a range observed in the study, and analyses in which informal care costs are excluded or included.

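### For patients who take the two-stage baseline, EQ-5D-5L may be collected after open allocation, yet it serves as time zero and as one of only two utility points in the QALY

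*Protocol article*

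**What the plan says.** The text under Fig. 1 in Data collection, management and analysis sets a conditional route: "If the patient appears to be burdened by the collection of baseline data we use a two-stage approach". On that route the article has "core data (Short IQ Code [14] and Confusion Assessment Method [9]) collected prior to randomisation and following consent". The Barthel Index, Charlson index and MoCA follow later, with "EQ-5D-5 L [12] and Health Resource Use Questionnaire) collected soon after randomisation".

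The Abstract describes a "multi-site randomised open trial of geriatrician-led admission avoidance hospital at home, compared with admission to hospital". Under Randomisation procedure and concealment of allocation, allocation is obtained "by a local member of the research team who accesses Sortition".

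In Table 1 the row "EuroQol five-dimension five-level (EQ-5D-5 L") is marked at baseline and at 6 months only. The Economic analysis section will "use linear interpolation between baseline and 6-month values and adjusting for within-trial mortality", and takes net cost per QALY gained within the trial as its main cost-effectiveness measure.

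**The concern.** A baseline utility is protected by randomisation only if it is taken before allocation is known. On the two-stage route it need not be. The patient, and probably the research nurse, may already know whether care will be at home or in hospital, and the trial compares exactly those settings. A self-rated health score can respond to that knowledge.

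Two distinct errors could follow:

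- **Reporting effect.** The rating differs between arms because allocation is known, although health does not differ.
- **Stretching.** Health really does differ in the first days. That difference belongs in the QALY, but only for as long as it lasts. Recorded as time zero, with the next measurement at 6 months, it is made to decline in a straight line over the whole half-year.

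Either error would enter the QALY difference, which is the denominator of the main cost-effectiveness measure.

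**Working it through.** The plan gives no expected QALY difference, so there is no figure of its own to reproduce. The check derives the weight of the baseline value from the stated rule.

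**Inputs from the article:** EQ-5D-5L at baseline and 6 months (Table 1); linear interpolation with an adjustment for death (Economic analysis); follow-up for the QALY of 0.5 years.

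**Assumed inputs:** f, the share of participants whose baseline EQ-5D-5L is taken after allocation, equal in the two arms; d, the between-arm gap in that value caused by allocation; no carry-over of d to the 6-month value. The article gives neither f nor d.

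**Step 1, weight for a survivor.** QALY = 0.5 x (U0 + U6)/2 = 0.25 U0 + 0.25 U6. Baseline and 6-month values have equal weight. Baseline's share of the QALY itself varies: 50% if U0 = U6, 40% at 0.4 and 0.6, 33% at 0.3 and 0.6.

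**Step 2, death at time t (years).** If utility is interpolated to zero at death (an assumption; the article does not give the method), QALY = t x U0/2. At 3 months this is 0.25 x U0/2 = 0.125 U0. The weight is below 0.25, but U0 is the only measured utility.

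**Step 3, shift in the arm difference.** Shift = 0.25 x f x d. The 2:1 ratio does not enter. With deaths, the shift is somewhat smaller than this survivor formula gives.

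| Share f | d = 0.02 | d = 0.05 | d = 0.10 |
|---|---|---|---|
| 10% | 0.0005 | 0.00125 | 0.0025 |
| 30% | 0.0015 | 0.00375 | 0.0075 |
| 50% | 0.0025 | 0.00625 | 0.0125 |
| 100% | 0.005 | 0.0125 | 0.025 |

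The 100% row is also the shift within the two-stage participants themselves. For scale, a true gap of 0.04 at 6 months alone (illustrative) gives 0.25 x 0.04 = 0.01 QALY under the same rule.

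**Step 4, stretching.** A real gap of 0.05 that fades linearly over 14 days is worth 0.05 x (14/365.25)/2 = 0.00096 QALY. The interpolation credits 0.25 x 0.05 = 0.0125, about 13 times as much. Fading over 7 days the ratio is about 26; over 28 days, about 6.5.

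**Step 5, would covariate adjustment repair it?** The article does not propose it, but it is an obvious response. With b the slope of U6 on U0, the slope of the QALY on U0 is 0.25(1 + b). After adjustment, with f = 100%, the remaining bias is 0.25d - 0.25(1 + b)d = -0.25bd. At d = 0.05 and b = 0.5 this is -0.00625. For a pure reporting gap, adjustment reverses the sign of the bias and does not remove it unless b = 0.

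**The case against.** The strongest reply is that the route is an exception, made deliberately for acutely ill older people, and that its use and its effect are both unknown. With a 10% share and a gap of 0.02 the shift is 0.0005 QALY. No direction can be given, no change in the cost-effectiveness conclusion is shown, and living at home at 6 months is untouched. All of this stands, and it limits the point to something the result can carry.

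A reader might go further and infer that the arms are already in different settings when EQ-5D-5L is completed. The article does not say so. Collection is described only as soon after randomisation, and patients referred by a general practitioner or seen in an assessment unit might answer before any move. Nor is the lack of a time limit held against the plan, because the participant timeline (Fig. 2) is not shown. Knowledge of allocation is enough for the concern.

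A reader might also infer that half of every participant's QALY is affected. One half is the interpolation weight for survivors with both values, and only those on the two-stage route are exposed.

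It is also fair that Table 1 already records place of assessment and difficulties in completing questionnaires at baseline, and that the handling of late values may be left to an analysis plan. Such a plan could add sensitivity analyses. It could not recover a pre-randomisation value that was never taken, and the order of collection is fixed in this article.

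Finally, setting late values to missing in the main analysis would be a doubtful remedy. For these patients the pre-randomisation data are little more than Short IQCODE, CAM and demographic or clinical items, so imputation would be weak.

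**Conclusion.** The point holds for two-stage participants. As written, the plan lets one of the two utility values behind its main cost-effectiveness measure be rated after open allocation, and then treats it as time zero. The possible shift in the arm difference is about 0.001 to 0.0125 QALY for an assumed share of 10 to 50% and an assumed gap of 0.05 to 0.10. It would be smaller with a smaller gap, and could go in either direction.

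The documents do not support the stronger statement that the cost-effectiveness result is biased, since they report neither the share nor any gap. This is an avoidable weakness in a secondary, economic analysis, worth correcting because correction is cheap and, according to Trial status, recruitment is still under way.

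**What to change.** **Collection (text under Fig. 1).** Add EQ-5D-5L to the core data taken after consent and before randomisation. The Barthel Index, Charlson index, MoCA and resource-use questionnaire can stay deferrable.

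**Values still taken after allocation.** Record date and time relative to randomisation, alongside the place of assessment already on the case report form, and ask the patient to rate the pre-randomisation state.

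**Economic analysis.** Keep late values in the main analysis. Add a sensitivity analysis that excludes them or replaces them with a common baseline imputed without using arm. This also covers participants already recruited by the two-stage route, as far as the timing of their assessment can be established.

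**Cost.** A few more minutes of questioning before randomisation for patients who already appear burdened, one added timing record, and one sensitivity analysis.

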**Fig. 2 Fig2:**
[figure not shown]
Participant timeline

At the 6-month follow-up point we collect data from all patients on mortality, new long-term residential care, cognitive impairment, activities of daily living, quality of life, length of stay, readmission or transfer to hospital, and on the number, type and duration of hospitalisations, the use of outpatient and day-case services, the use of community-based health care services including general practitioner consultations and practice-based nursing, medications, respite care, social care including admission to residential or nursing home, and amount of informal care received over the preceding 6 months. Unit costs will be attached to these resource volumes, using National Health Service (NHS) reference costs, Unit Costs of Health and Social Care (PSSRU), and other national data sources. We will collect the costs of the admission avoidance hospital at home intervention in collaboration with providers, and include training time and other elements. This is likely to vary between centres and we aim to collect cost information from all participating centres if possible. At 12 month follow-up we will collect data on living at home (Table 1).

**Table 1 Tab1:** Case report form

	Study period					
	Baseline	Day 3	Day 5	1 month	6 month	12 month
ENROLMENT						
Eligibility screen	X					
*Informed consent*	X					
*Screening log*	X					
Randomisation	X					
ASSESSMENT						
Assessment form	X	X	X	X	X	X
*Demographics*	X					
*Presenting problem*	X					
*Place of assessment*	X	X	X	X	X	X
*Patient status* (*‘living at home’*)		X	X	X	X	X
*Subsequent admissions*				X	X	
Adverse event log		X	X	X	X	X
QUESTIONNAIRES						
Barthel Index of Activities of Daily Living	X				X	
Confusion Assessment Method (CAM)	X	X	X	X		
Charlson Co-morbidity Index	X				X	
Health Service Use Questionnaire	X				X	
Short Form of the Informant Questionnaire on Cognitive Decline in the Elderly (Short IQCODE)	X					
Montreal Cognitive Assessment (MoCA)	X				X	
EuroQol five-dimension five-level (EQ-5D-5 L)	X				X	
Patient feedback form				X		
Difficulties in Questionnaire completion Form	X	X	X	X	X	
MISCELLANEOUS						
Death form	Completed on patient death					
Discontinuation form	Completed when a patient withdraws or is lost to follow-up					

### Process evaluation

We will complete a structured pro forma to record the key features of the organisation and delivery of admission avoidance hospital at home and of inpatient care, and any local changes to policy and implementation. This will include reviewing care protocols, the method of assessing the patient, and conversations with the staff delivering the intervention. Once recruitment to the trial is established approximately six patients and their carers (until data saturation), from two or more hospital at home and inpatient settings, will be invited to be interviewed at the point of discharge or immediately after discharge from their healthcare setting. Patients and carers will be selected to include those with cognitive impairment, those who are physically frail and who have experienced varied types of health crises (sudden onset of chronic illness, deterioration in the context of multiple health problems and acute exacerbation of a chronic condition) that will impact on the recovery process. The interviews will assess the process of care and how the healthcare they received facilitated recovery, as well as relatives/caregivers perceptions and experience of HAH and inpatient care. Interviews will be recorded. We will also complete a structured pro forma to record the key features of the HAH with CGA intervention and of inpatient care, this will include the use of care protocols, the method of assessing the patient, and conversations with the staff delivering the intervention.

### Data management

We store all paper and electronic data in a secure environment, and refer to the participant by a trial number and not by name, except for the signed consent form. We follow the standard operating procedures of the University of Oxford Primary Care Clinical Trials Unit, which are fully compliant with the Data Protection Act and Good Clinical Practice (GCP). No-one outside the study team has access to either the CRFs or the database; members of the research team can access patient identifiable data in order to collect follow-up data. Direct access will be granted to authorised representatives from the sponsor and host institution for monitoring and/or audit of the study to ensure compliance with regulations. Staff at each site enters data directly to a secure laptop or computer or on paper versions of the CRF and questionnaires. Data from paper forms are double entered. Researchers from each site are asked to check data for completeness prior to returning, for those sites entering data directly into the database internal validation checks are run for each data field. Any inconsistencies and missing data are highlighted as queries which are then returned to the site to be resolved. With regards paper CRFs, the same checks are applied once the data managers have performed the double data entry. Data queries are returned to sites for resolution on a regular basis. Interviews will be audio recorded, fully transcribed and entered into NVivo software. Field notes pertaining to the physical, social and care environment of the home setting will also be managed and analysed. All audio recordings and field notes will be stored safely in confidential conditions and electronic data in a secure, protected environment.

#### Study oversight

The overall supervision of the trial is carried out by the Trial Steering Committee. An independent Data Monitoring Committee meets every 6 months to review trial progress and data, this includes all SAE reports. The sponsor is the University of Oxford.

### Statistical methods

#### Sample size

We calculated the sample size for the primary outcome ‘living at home’ (the inverse of death or living in a residential care setting) at 6 months follow-up, for a 2:1 randomisation ratio with two-thirds randomised to admission avoidance hospital at home and one-third to inpatient admission. Several sources informed our estimate of effect size, these included an audit of 750 patients who received admission avoidance hospital at home in Lanarkshire, and the summary estimate from a Cochrane Review of admission avoidance hospital at home that was published in 2008 [16]. Our proposed study effect estimate is based on a control group (inpatient admission) event rate at 12 months of 50% living in a residential setting, with a 10% reduction to 40% in the admission avoidance hospital at home group, equal to a relative risk of 0.8 which lies towards the top end of the 95% confidence interval (CI) for the pooled estimate reported in the Cochrane Review [16]. We have calculated that to achieve 90% power at a significance level of 0.05, we will need to recruit 1350 participants to detect a 10% absolute difference. The estimated recruitment rate allows 15% attrition resulting in a projected sample size of 1552. We have re-examined the sample size calculation using an estimate of the intra-cluster correlation (ICC) of 0.005, this would provide 88% power to detect the assumed effect size of RR = 80%, for a two-tailed alpha of 0.05.

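### The sample size of 1350 does not follow from its stated inputs (about 1164 to 1209 analysed gives 90% power), and it is unclear whether 1350 already includes attrition

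*Protocol article*

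**What the plan says.** All the figures are in the Sample size section of the protocol article.

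- Allocation: "for a 2:1 randomisation ratio with two-thirds randomised to admission avoidance hospital at home and one-third to inpatient admission".
- Control rate: "control group (inpatient admission) event rate at 12 months of 50% living in a residential setting".
- Effect: "with a 10% reduction to 40% in the admission avoidance hospital at home group, equal to a relative risk of 0.8".
- Requirement: "to achieve 90% power at a significance level of 0.05, we will need to recruit 1350 participants". The verb is recruit; the number to be analysed is not given separately.
- Sidedness appears only in the later sentence on intra-cluster correlation: "for a two-tailed alpha of 0.05".
- Attrition: "The estimated recruitment rate allows 15% attrition resulting in a projected sample size of 1552".

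The section ends by re-examining the calculation with an intra-cluster correlation (ICC) of 0.005 and reports 88% power. It does not say which number of participants or which design effect gives that 88%.

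**The concern.** The section offers a chain of numbers: inputs, then 1350, then 1552, then 88% power. The first link does not reproduce, and the second uses a shortcut that does not preserve the number it is meant to protect. A reader cannot tell whether 1350 is the number needed in the analysis or a recruitment figure that already allows for loss.

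This matters because recruitment is ongoing (Trial status) and an independent Data Monitoring Committee reviews progress every six months (Study oversight). If recruitment lagged, the committees would want to know which number delivers the planned power. The article points to 1350 or 1552, while its own inputs point to about 1164 to 1209 under a simple test. The closing sentence gives a power already below 90% without saying at what N.

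**Working it through.** **Inputs**, all from the Sample size section: p1 = 0.50 (control), p2 = 0.40 (hospital at home), allocation k = 2 to 1, power 90%, alpha 0.05. The two-tailed alpha of the ICC sentence is taken to apply to the main calculation as well. The rates are taken as printed, although they are given at 12 months and the primary outcome is at 6 months.

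**Step 1: number for 90% power.** Pooled-variance two-proportion test, control-arm size:

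n = [z(0.975)·√(p̄q̄(1 + 1/k)) + z(0.90)·√(p1q1 + p2q2/k)]² / (p1 − p2)²

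- p̄ = (0.50 + 2 × 0.40)/3 = 0.4333, so p̄q̄ = 0.2456.
- First term: 1.960 × √(0.2456 × 1.5) = 1.960 × 0.6069 = 1.1895.
- Second term: 1.2816 × √(0.25 + 0.12) = 1.2816 × 0.6083 = 0.7795.
- n = (1.1895 + 0.7795)²/0.01 = 387.7, rounded up to 388 control. The total is 388 + 776 = **1164**.
- With continuity correction: 403 control, total **1209**.

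**Step 2: can the printed 1350 be reproduced?**

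| Variant (90% power) | Total |
|---|---|
| Two-sided, 2:1, pooled | 1164 |
| Two-sided, 2:1, unpooled, arcsine or log odds ratio | 1167 |
| Two-sided, 2:1, log relative risk | 1110 |
| Two-sided, 2:1, continuity-corrected | 1209 |
| One-sided, 2:1, without / with continuity correction | 951 / 993 |
| Two-sided, 1:1, without / with continuity correction | 1038 / 1076 |

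None reaches 1350. It exceeds 1209 by 141 (1350/1209 = 1.12) and 1164 by 186 (1350/1164 = 1.16).

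**Step 3: power if 1350 are analysed.** The control arm is 450. (0.1 × √450 − 1.1895)/0.6083 = (2.1213 − 1.1895)/0.6083 = 1.532, so power is **93.7%**.

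**Step 4: does 1350 already contain attrition?** 1164 × 1.15 = 1339 and 1164/0.85 = 1370, so 1350 lies between them and equals neither. Read as a recruitment figure, 1350 × 0.85 = 1147.5 analysed, with 89.6% power, close to the printed 90%. That fits the reading but does not prove it. Starting from 1209, the same two operations give 1390 and 1423, both above 1350.

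**Step 5: the attrition step.**

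- 1350 × 1.15 = 1552.5, which reproduces the printed 1552.
- To keep 1350 after 15% loss: 1350/0.85 = 1588.2, rounded up to 1589. The shortfall is 1589 − 1552 = 37 (2.3%).
- Loss that 1552 tolerates while keeping 1350: 1 − 1350/1552 = 13.0%.
- 1552 × 0.85 = 1319 analysed, with **93.2%** power under the simple test.
- Loss that 1552 tolerates before falling below 1209 or 1164: 1 − 1209/1552 = 22.1%, or 1 − 1164/1552 = 25.0%.

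**Step 6: the 88%.** Under the simple test, 88% power corresponds to about 1088 independent participants. That implies a design effect of 1350/1088 = 1.24 if the base is 1350, or 1552/1088 = 1.43 if it is 1552. The article states neither the base nor the design effect, so the 88% cannot be tied to a number.

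**The case against.** The strongest reply is that the errors are harmless. The first makes the trial larger than its inputs require, and the second is a common shortcut that misses by 37 participants. This stands. A reader might infer from the attrition step that 1552 fails to allow for 15% loss, or that the trial is underpowered. The document does not support either inference. The shortfall exists only against 1350 as an analysed target; against the 1164 to 1209 that the inputs require, 1552 absorbs 15% loss with room to spare. It also goes too far to say that 1552 has no derivation, since it follows from 1350 by multiplying by 1.15.

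A second reply is that 1350 is called the number to recruit, so it may never have been the analysed target. That is a fair reading, and the complaint that 1319 is below 1350 then falls away. But 1350 would then already include loss, and the step to 1552 would add it again. A reader might conclude outright that attrition was counted twice. The arithmetic is only compatible with that; the article does not say so.

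A third reply is that clustering explains the larger number. It does not, because the ICC enters afterwards, as a re-examination of a calculation already made. The reply does carry one valid warning. The figures above assume independent observations at one time point, whereas the Analysis section plans a mixed-effect logistic model with random effects for centre and participant. They should not be called the trial's true power.

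**Conclusion.** The point holds in a limited form. As the number for 90% power, 1350 is 12% to 16% above what the stated inputs give under a simple two-proportion test (1164, or 1209 with continuity correction). If 1350 is the number analysed, the power is about 94%. The attrition step is a lesser slip: 37 participants (2.3%) short of 1589, and only if 1350 is the analysed target. On neither reading of 1350 are all the printed figures right together.

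Neither error takes the trial below 90% under the simple test, since 15% loss from 1552 leaves 1319 and about 93%. This rests on the printed 50% and 40%, two-sided 0.05, 2:1 allocation and independent observations. A reader might take 1164 to 1209 as a sufficient number for this trial. The document does not support that: its own ICC-adjusted power is 88%, at an unstated N, and the planned analysis adjusts for centre. The matter is one of clarity and internal consistency, not of an inadequate trial.

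**What to change.** Correct the text of the Sample size section; no extra recruitment and no change to the analysis is needed.

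1. State whether 1350 is the number analysed or the number recruited, and give its power under the stated inputs. If analysed, that is about 94%, with 90% reached at 1164 (1209 with continuity correction). If recruited with 15% loss already included, say so and give the analysed number: 1350 × 0.85 is about 1148, with power just under 90%.
2. Apply attrition once, by dividing by 0.85. If 1350 is the analysed target, either give 1589 or keep 1552 and say that it tolerates 13.0% loss. If 1350 already includes loss, describe 1552 as a margin above it.
3. State which N, which design effect and which centre sizes give the 88% power at an ICC of 0.005, and say that the simple-test figures are not a sufficient number under the centre-adjusted analysis.

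The cost is a few sentences and a check of the original calculation file.
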